### Randomisation, allocation concealment and blinding procedure

Participants will be randomised into one of the treatment groups using a computer-generated randomisation table once written consent has been obtained and the baseline assessments have been completed. Clinicians from participating mental health services will inform potential participants about the study. If interested and agreeing to be contacted, a member of the research team who is independent of the person’s clinical care will communicate further details about the study with the potential participant. If still wishing to participate, consent from participants will be obtained by the researcher. Their capacity to understand the risks and benefits of participation will be assessed on an ongoing basis in compliance with Australian National Health and Medical Research Council guidelines regarding ethical conduct in human research. Participants will receive either active treatment (1000, 2000 or 4000 mg/day) or placebo in a 1:1:1:1 ratio.

The randomisation will be double-blind. An independent biostatistician will generate the randomisation list which will be provided to the manufacturer and to the Princess Alexandra Hospital Pharmacist. All medication will be blinded to the study personnel (including data analysts), research pharmacist and the patient. Sodium benzoate and placebo capsules will be identical in terms of packaging, appearance, colour and taste. Treatment allocations will not be disclosed to the Investigator or any study personnel before the database is locked, unless in an emergency which requires unblinding.

### Unblinding

Only in the event of a medical emergency which the Investigator feels cannot be adequately managed without knowing the identity of the study medication, will the treatment code be unblinded for a particular participant. In such an event, this would be done by the Princess Alexandra Hospital Pharmacist via a 24-h number. All cases of emergency unblinding will be documented on a Serious Adverse Event Form and reported to the sponsor within 24 h. Unblinded participants will be withdrawn from the study.

### Drug administration

The study medication will be compounded by Optima Ovest Pty Ltd. The medication for the active arms (1000, 2000 and 4000 mg/day) will consist of 4 doses of sodium benzoate (125 mg, 250 mg and 500 mg) in identical capsule form to be taken twice/day. The placebo will consist of microcrystalline cellulose in a matched gelatine capsule. Prior to dispensing, all study medication will be kept at the Queensland Centre for Mental Health Research, only accessible to delegated members of the study team. Dispensing to participants will occur once consent has been obtained and after the screening phase and randomisation has occurred. The study medication will be dispensed on a fortnightly basis by delegated research staff in accordance with Fig. 1*.* Compliance with study medication will be calculated at each visit by means of self-report and a capsule count. This data will be used to calculate compliance with medication for analysis purposes.

**Fig. 1 Fig1:**
[figure not shown]
Schedule of visits and assessments. *PANSS* Positive and Negative Syndrome Scale, *GAF* Global Assessment of Functioning, *CGI* Clinical Global Impression, *PGI* Patients’ Global Impression of Improvement

### Dose justification

With respect to the choice of doses of sodium benzoate to examine, Lane et al. [22] reported clinical efficacy with 1000 mg per day whilst Lin et al. [23] reported benefits of 2000 mg sodium benzoate per day that were larger than those from 1000 mg per day. No studies in people with schizophrenia have used doses of 4000 mg per day. Limited side effects are seen in the use of very high doses of up to 500 mg/kg/day in patients with urea cycle disorders [36] which gives us confidence to prescribe up to 4000 mg per day for the purposes of establishing the most appropriate dose for the treatment of schizophrenia.

### Comparator justification

The comparator condition in this study consists of placebo in addition to routine care. The Declaration of Helsinki affirms that placebo-controlled trials should only be used in the absence of existing proven therapy [39]. Therefore, the use of an adjunct therapy has been selected to ameliorate these ethical concerns as both the experimental and control groups will receive standard medical care (Treatment as Usual).

### Outcome measurement

Clinical measures of disease severity and physical health and biochemical samples will be taken at baseline and afterwards according to Fig. 1.

### Clinical outcome measures

The severity of schizophrenia symptoms as measured by the Positive and Negative Syndrome Scale (PANSS) total score will be the primary continuous outcome measure. The mean change in scores from baseline to week 6 (end of the study) will be compared between study arms.

Average change in scores from baseline to week 6 (end of the study) in the following secondary clinical outcome continuous measures will also be included:
PANSS subscale scores, reflecting the severity of positive and negative symptoms and general psychopathology.Global Assessment of Function (GAF), a numeric scale (1 through 100) used by physicians to rate subjectively the social, occupational, and psychological functioning of adults.Clinical Global Impression (CGI) which is used to measure symptom severity, treatment response and the efficacy of treatments in treatment studies of patients with schizophrenia.Patient Global Impression (PGI) is a global index that is used to rate the response of a condition to a therapy (transition scale).

### Biomarkers

To investigate biochemical activity associated with sodium benzoate treatment a 25-mL sample of blood will be taken from consenting participants via venipuncture at baseline and week 6. Pathology Qld will be responsible for collecting, storing, and analysing blood samples. The biomarkers examined between study arms will include the average concentration of (1) plasma amino acids (D-alanine, L-alanine, D-serine, L-serine, glycine, glutamine and glutamate) and (2) plasma sodium benzoate. To assess for changes in oxidative stress, plasma catalase, 3-nitrotyrosine and malondialdehyde will be measured to determine whether sodium benzoate has a related mechanism of action, as suggested by a previous animal study [28] and human clinical trial [23]. It has been proposed that oxidative stress is involved in both the onset and the persistence of schizophrenia [30]. Average change in inflammatory response activity will be assessed by high-sensitivity CRP. Previous trials have not observed changes in D-amino acid concentration following sodium benzoate admission at 1000 mg and 2000 mg, inconsistent with the original hypothesised mechanism of action of the compound [23, 24]. Comparison of changes from baseline to week 6 (end of the study) in these biomarkers will allow us to observe whether administration of higher doses of sodium benzoate are needed to observe changes in peripheral amino acids. Participants refusing to for biological samples to be collected and stored can still participate in the trial.

### Compliance monitoring and adherence

After commencing the trial, participant’s adherence to medication will be assessed each week either through face-to-face visits or via phone. Participants will also be instructed to return any unused study medication and empty bottles to delegated research assistants. Assessment of compliance will be calculated by self-report and capsule count. Any identified issues with medication compliance will be discussed at weekly team meetings. To assist with participant compliance, a meals-reminder aid will be given with the study medication.

### Case report form

A case report form (CRF) will be completed for each study participant summarising all clinical screening and study data for analysis. In the CRF, participants will only be identified by their participant number in order to retain participant confidentiality.

The completed case report forms (CRF’s) will be retained by the Investigators for a period of at least 15 years or the maximum time frame as determined by local regulations, whichever is the longest.

### Study restrictions

There are no restrictions to participants during the study in terms of concomitant medication, exercise or ambulation.

### Safety assessments

All patients recruited in this study will be receiving care at either Metro North Hospital and Health Service or West Moreton Hospital and Health Service. The study team will liaise with clinical staff to ensure that participants have undergone a routine physical health screen. If a participant is of child-bearing potential and sexually active, urine pregnancy tests will be conducted at baseline and when clinically appropriate.

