### Safety profile of sodium benzoate

The safety of sodium benzoate has been studied extensively because it has been widely used as a food preservative, in cosmetics and also as a medication. The US Food and Drug Administration has classified sodium benzoate as ‘Generally Recognized As Safe’ and regulates the concentration of sodium benzoate to 0.1% by weight in food products and 1% concentration in medicines [31, 32]. The joint committee by the Food and Agriculture Organization of the United Nations and the World Health Organization has suggested an acceptable daily intake of 0.5 mg/kg of body weight [33].

The International Programme on Chemical Safety (IPCS) published a report on sodium benzoate (and a related compound benzoic acid) detailing the potential health effects of sodium benzoate in animal studies. Testing in rodents revealed a low rate of toxicity with mean lethal dose (LD50) values of > 1940 mg/kg body weight. Drawing evidence from two long term studies (12–16 months) in rodents, there was no evidence to suggest sodium benzoate had carcinogenic properties. Likewise, studies of the precursors of benzoic acid–benzyl acetate, benzyl alcohol, and benzaldehyde suggest that a carcinogenic effect of sodium benzoate is unlikely. The results of genotoxic activity were inconclusive in the IPCS report, and there were no consistent abnormal findings based on the Ames test. Based on in vitro studies of human lymphoblastoid cell lines, the evidence suggests that sodium benzoate at very high concentrations does have genotoxic effects. Sodium benzoate does have embryotoxic and fetotoxic effects; however, these are only evident at dosage levels high enough to cause severe maternal toxicity. A No Observable Adverse Effect Level (NOAEL) of approximately 1310 mg/kg body weight for teratogenic effects in rodents was established [34].

The acute toxicity of oral sodium benzoate in humans is low. There is evidence that some atopic individuals may be sensitive to food additives and preservatives (benzoate is a food preservative) [35]. The safety of sodium benzoate  reported in three trials of people with psychosisshowed no increase in reported side effects in participants who received sodium benzoate compared to placebo [22–24].

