### Inclusion and exclusion criteria

Patients will be invited to participate in the study if they meet all of the following criteria:
Aged between 18 and 64 years (inclusive).Fulfil the DSM-IV criteria for schizophrenia, based on the Diagnostic Interview for Psychosis.Met diagnostic criteria for schizophrenia for at least 12 months duration.PANSS total score ≥70.Received antipsychotic medications for a period of at least one continuous month prior to assessment for the study and remained symptomatic despite the medications.Agreed to participate, has capacity to consent and is able to follow the study instructions and procedures.

Patients will be excluded from the study if they meet any one of the following criteria:
Known allergies to sodium benzoate (E211) or any part of the formulation of the investigational product.Suspected allergies or known adverse reactions to food preservatives in general.Unable to understand or communicate in English.For female participants, those currently pregnant, or planning to become pregnant or lactating during the study period or are sexually active and using ineffective contraception.Inability to follow the study instructions and procedures.

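### The stated pregnancy test covers only participants of child-bearing potential who are also sexually active, so some women can be randomised untested although every current pregnancy is an exclusion

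*Protocol article*

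**What the plan says.** The exclusion criteria (Inclusion and exclusion criteria) list: "For female participants, those currently pregnant, or planning to become pregnant or lactating during the study period or are sexually active and using ineffective contraception". Current pregnancy stands there without any condition. Sexual activity qualifies only the last limb, on contraception.

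Safety assessments gives the testing rule: "If a participant is of child-bearing potential and sexually active, urine pregnancy tests will be conducted at baseline and when clinically appropriate". The sentence before it says: "The study team will liaise with clinical staff to ensure that participants have undergone a routine physical health screen". What that screen contains is not described.

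Under Randomisation, allocation concealment and blinding procedure, a participant is randomised "once written consent has been obtained and the baseline assessments have been completed". Under Drug administration: "Dispensing to participants will occur once consent has been obtained and after the screening phase and randomisation has occurred". Neither section names a negative pregnancy test as a condition. Participant withdrawal makes a confirmed pregnancy a reason to withdraw, but adds no test.

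**The concern.** The check is narrower than the exclusion it serves. Present sexual activity is a poor filter for present pregnancy. A woman whose activity stopped some weeks ago can truthfully be classed as not active and still be pregnant. The classification also depends on a sensitive self-report, where a urine test would answer the question directly.

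At stake is exposure of an undetected pregnancy to study drug. Three of the four arms are active, and Dose justification says of the top dose: "No studies in people with schizophrenia have used doses of 4000 mg per day". Nothing statistical is at stake: sample size, power, alpha and the primary analysis do not depend on this rule.

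**Working it through.** **Comparing the rules**

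| Step | Section | Who is covered |
|---|---|---|
| Exclusion for current pregnancy | Inclusion and exclusion criteria | All female participants |
| Exclusion for ineffective contraception | Inclusion and exclusion criteria | Sexually active female participants |
| Urine pregnancy test | Safety assessments | Child-bearing potential **and** sexually active |
| Condition for randomisation | Randomisation section | Consent and baseline assessments; no pregnancy test named |
| Withdrawal on confirmed pregnancy | Participant withdrawal | All; no test added |

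The two conditions open the testing sentence, so they govern both the baseline test and the later tests. A woman of child-bearing potential classed as not sexually active falls under the first row but not the third, and nothing in the fourth row stops her.

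**How many women**

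From the article: 52 participants, allocated 1:1:1:1. Assumed, because the article gives no figures: 25–40% are women of child-bearing potential, a third to a half of those are classed as not sexually active, and 0.1–0.5% of those have an undetected pregnancy.

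- Women of child-bearing potential: 0.25 × 52 = 13 to 0.40 × 52 = 20.8.
- Untested: 13 / 3 = 4.3 to 20.8 / 2 = 10.4. Mid-range: 17 × 0.42 = 7.1, about 7.
- Untested and on active drug (3 of 4 arms): 7 × 0.75 = 5.3; range 4.3 × 0.75 = 3.2 to 10.4 × 0.75 = 7.8.
- Untested and on 4000 mg (1 of 4 arms): 7 × 0.25 = 1.8; range 4.3 × 0.25 = 1.1 to 10.4 × 0.25 = 2.6.
- Expected missed pregnancies, 7 women: 7 × 0.001 = 0.007 to 7 × 0.005 = 0.035.
- Expected missed pregnancies, number untested and prevalence varied together: 4 × 0.001 = 0.004 to 10 × 0.005 = 0.05.

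**How large the dose is against the animal data**

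Safety profile of sodium benzoate states: "A No Observable Adverse Effect Level (NOAEL) of approximately 1310 mg/kg body weight for teratogenic effects in rodents was established". The body weight of 70 kg is the one the article uses for its urea cycle dose range. The comparison is plain mg/kg, with no scaling between species.

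| Daily dose | mg/kg at 70 kg | 1310 ÷ mg/kg |
|---|---|---|
| 1000 mg | 1000 / 70 = 14.3 | about 92 |
| 2000 mg | 2000 / 70 = 28.6 | about 46 |
| 4000 mg | 4000 / 70 = 57.1 | about 23 |

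**The case against.** The strongest reply is that nothing contradicts anything. One section sets who is excluded, another sets who is tested, and the two groups need not be the same. A known or reported pregnancy is excluded whatever the sexual history. Selecting women for testing by history can be a deliberate, risk-based choice. The article never says the urine test is the only way to apply the exclusion, and the routine health screen might pick up a pregnancy. This much stands: the gap is in verification, and the protocol does not permit enrolling a woman known to be pregnant.

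It can also be said that this is a condensed article. The content of the screen, and any definition or look-back period for sexual activity, may sit in the full protocol, and the schedule of assessments in Fig. 1 is not visible. That is fair for those details, and their absence is not held against the plan. It does not answer the main point, because the article states in words who is tested, and that statement is too narrow.

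The risk is low. On embryo-fetal effects the article says: "Sodium benzoate does have embryotoxic and fetotoxic effects; however, these are only evident at dosage levels high enough to cause severe maternal toxicity". It also reports long-term use of 250–500 mg/kg per day in urea cycle disorders with rare toxicity; 57.1 mg/kg is 11% of 500 and 23% of 250. Exposure lasts six weeks. All of this stands and limits the severity. It does not explain why a pregnancy exclusion should be verified by test in some women of child-bearing potential and not in others.

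Finally, every share used in the count is an assumption. That also stands. The case rests on the mismatch between the two rules and the low cost of closing it, not on the expected yield.

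**Conclusion.** The point holds at the lowest severity, as a cheap safety improvement. The stated test is narrower than the stated exclusion, and a woman of child-bearing potential classed as not sexually active can reach randomisation and dosing untested. On the assumed shares about 7 women (range 4–10) would be affected, about 5 of them on active drug and about 2 on 4000 mg. The expected number of missed pregnancies is far below one; even the upper figure of 0.05 is one in about 20 such trials. These counts would change with the true mix of participants, but the mismatch between the rules would not.

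**What to change.** Amend the testing sentence in Safety assessments along these lines: *A urine pregnancy test will be done at baseline for every participant of child-bearing potential, whatever sexual activity is reported, and the result will be known before randomisation; further tests will be done when clinically indicated.*

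Randomisation already follows the baseline assessments, so the order of events does not change; what is new is the wider group tested and the explicit requirement for a result. The withdrawal rule for confirmed pregnancy can stay as it is, since it does not depend on reported sexual activity.

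The cost is one amended sentence and about 7 extra urine tests (range 4–10, same assumptions), using a test and a visit already in the protocol. Sample size, visits, withdrawal rules and analysis are unchanged.

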### Adverse events

The Investigator and designated study personnel will monitor each participant for adverse events during the study. All adverse events reported between consent and final follow-up visit will be recorded in the case report form (CRF). The investigator or designee will ask the participant non-leading questions in an effort to detect adverse events e.g. ‘Have you felt unwell or different in any way since your last visit’.

In addition, participants will be encouraged to spontaneously report any unusual feelings or sensations. Adverse events will be continuously monitored. Serious adverse event (death, life-threatening illness or incident, hospitalisation or any event deemed by the principal investigator to be a significant medical event) will be reported to the study sponsor, ethics committees and governance bodies and the DSMB within 24 h of notification of the incident. An assessment of causality from the investigational product for the serious adverse event will be completed at the time of notification.

### Participant withdrawal

All participants have the right to withdraw consent at any time without prejudice and this will not affect their ongoing care. This will be clearly discussed during the consenting process. If a participant decides to withdraw consent, we will complete a revocation of informed consent form.

Participants will be withdrawn from the study by the Investigator, prior to completion of treatment, under the following conditions:
Non-compliant with study medication for seven consecutive daysNon-adherence of more than 50% of study medication on capsule countDevelopment of a serious adverse event assumed to be associated with the study medicationCessation of effective contraception or confirmed pregnancyContinual inability to provide informed consent.

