### Study design

The design is a randomised, placebo-controlled, double-blind parallel-group trial to determine the dose of sodium benzoate required for add-on treatment of patients with treatment-refractory schizophrenia. The study is a phase II dose-finding study with secondary endpoints which comprise a pharmacokinetic/pharmacodynamics investigation. This study will include 52 individuals with treatment-refractory schizophrenia. Patients will be given 1000 mg (500 mg bd), 2000 mg (1000 mg bd) or 4000 mg (2000 mg bd) daily of sodium benzoate or placebo. Participants will receive either active treatment (1000, 2000 or 4000 mg/day) or placebo in a 1:1:1:1 ratio. This study medication will be in addition to participants’ routine care, defined as ‘individualized combinations of psychopharmacology, behavioural interventions, rehabilitation and associated clinical services’ in keeping with Queensland Health standards of care. Face-to-face clinical assessments will be at baseline (week 0) and weeks 2, 4 and 6. Weekly phone contact will occur in weeks between face-to-face visits. The SPIRIT reporting guidelines have been used in this study protocol and a spirit checklist has been completed [38].

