### Sample size justification

The primary analysis will be a mixed effect repeated measures analysis comparing total PANSS scores across 4 time points (baseline, 2, 4, and 6 weeks) across 4 dose groups (placebo, 1000 mg, 2000 mg and 4000 mg per day). A recent study by Scott et al. [24, 26] observed a standard deviation for total PANSS score of around 15 for all subjects, and closer to 10 for cases with baseline PANSS scores > 75. The autoregressive (AR(1)) correlation between weeks was estimated at 0.815. Assuming a decrease in PANSS scores similar to this previous study, this study has at least 80% power to detect an effect size of 0.55 between treatments with a sample size of 52 participants, incorporating an allowance for 20% attrition.

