### Statistical analysis

We will compare demographic and clinical differences between the groups at baseline (Fisher exact test for nominal variables and Mann-Whitney test or independent sample t test for continuous variables). All data will be analysed, regardless of whether participants withdrew spontaneously or were withdrawn by the investigator. Efficacy will be assessed according to standard Intention to Treat (ITT) analytic procedures (i.e. for those who do not complete the 6-week study period, we will carry forward their last observation on the study outcomes). A secondary analysis will also be conducted including participants who (1) were in the trial for all 6 weeks, (2) were treatment adherent ≥80% and (3) had no other major protocol violations. Missing values will be addressed using a mixed-effects model repeated measures analysis which is robust in maintaining statistical properties of tests. Mean changes in clinical assessment will be assessed using mixed-model repeated-measure (MMRM) methods with treatment, week, and treatment-week interaction as fixed effects and intercept as the only random effect; baseline value will be the covariant. *P* values will be based on 2-tailed tests with significance levels of 0.05 corrected for multiple comparisons. A more detailed statistical analysis plan will be finalised before database lock.

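### Investigator withdrawal removes participants from the study, not only from study medication, so the later PANSS scores that the ITT comparison needs are not collected

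*Protocol article*

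**What the plan says.** Five places in the protocol article bear on this.

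- **Participant withdrawal:** "Participants will be withdrawn from the study by the Investigator, prior to completion of treatment, under the following conditions". The list covers seven days of non-compliance in a row, more than 50% non-adherence on capsule count, and a serious adverse event presumed related to study medication. It also covers stopping effective contraception or pregnancy, and continuing inability to give informed consent.
- **Unblinding:** after emergency code-breaking, "Unblinded participants will be withdrawn from the study".
- **Clinical outcome measures:** for PANSS total, "The mean change in scores from baseline to week 6 (end of the study) will be compared between study arms".
- **Study design:** "Face-to-face clinical assessments will be at baseline (week 0) and weeks 2, 4 and 6".
- **Statistical analysis:** "All data will be analysed, regardless of whether participants withdrew spontaneously or were withdrawn by the investigator". The ITT procedure is then described: "for those who do not complete the 6-week study period, we will carry forward their last observation on the study outcomes". The same section assigns missing values to a mixed model for repeated measures. It also defines a separate analysis: "A secondary analysis will also be conducted including participants who (1) were in the trial for all 6 weeks, (2) were treatment adherent ≥80"%, with no other major protocol violations.

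Nowhere does the article distinguish stopping study medication from leaving outcome follow-up.

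**The concern.** An ITT comparison asks what happens to everyone as randomised, including those who take the capsules poorly or stop. Those are the people the withdrawal rules remove from the study. Once they are removed, the article gives no route by which their remaining PANSS assessments are obtained, and the primary comparison depends on week 6.

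The triggers occur after randomisation. Poor adherence and related serious events may differ by dose, and may go with how the participant is doing. If so, the missing scores are informative and can differ between arms of 13 (52/4). The investigator creates this missingness by rule, in people who may be willing to be assessed.

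A statistical analysis plan written later can choose how to model missing scores. It cannot recover scores that were never taken.

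**Working it through.** **1. When each trigger can act.** Adherence is checked every week by visit or phone (Compliance monitoring and adherence), and capsules are counted at each visit (Drug administration).

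- The seven-day rule can therefore act at week 1, before any post-baseline PANSS, so the last observation would be the baseline score.
- The capsule-count rule can act at week 2, with weeks 4 and 6 then lost.
- Any trigger after week 4 loses week 6, the primary time point.

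**2. What the analysis section protects.** The promise to analyse all data regardless of withdrawal covers data already collected. Carrying forward for those who do not complete six weeks presupposes that their week-6 score is absent. The reimbursement section points the same way: it ties payments to visits and allows pro-rata payment for anyone withdrawn early.

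**3. The plan's own sample size.** The plan claims that "this study has at least 80% power to detect an effect size of 0.55 between treatments with a sample size of 52 participants", including 20% attrition. If 0.55 is read as Cohen's f in a four-group one-way ANOVA at two-sided 0.05, 80% power needs N = 41, and 41/0.80 = 51.25, rounded up to 52. The article does not name the metric, so the match depends on that reading. The allowance means 0.20 × 52 = 10.4 participants without a week-6 score. On this reading power is 0.821 with 42 analysed and 0.907 with 52. That gap is a ceiling on what fuller follow-up could return, because the 20% also covers people who withdraw consent or are lost.

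**4. Can the bias be signed?** Illustrative assumptions, not from the document:

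- The week-6 effect is D and grows linearly over six weeks.
- A share p = 0.20 of an active arm is withdrawn and none of the placebo arm.
- There is no background trend.
- f is the fraction of six weeks elapsed at the last visit.

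Carrying forward estimates D × [1 − p(1 − f)]. A mixed model under missing-at-random tends towards D.

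| Last visit | f | Carried forward | Truth if benefit is lost after stopping | Truth if benefit continues |
|---|---|---|---|---|
| Week 0 | 0 | 0.80 D | 0.80 D | 1.00 D |
| Week 2 | 1/3 | 0.87 D | 0.80 D | 1.00 D |
| Week 4 | 2/3 | 0.93 D | 0.80 D | 1.00 D |

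If benefit is lost, carrying forward is 0%, 8% or 17% too high (0.867/0.80 = 1.083; 0.933/0.80 = 1.167), and the mixed model up to 25% too high (1/0.80). If benefit continues, carrying forward is 20%, 13% or 7% too low and the mixed model is about right.

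Now add a linear background improvement T by week 6 in both arms, with benefit lost. The error of carrying forward becomes p × [f·D − (1 − f)·T]. With the last visit at week 2 this is zero at T = 0.5 D and negative above that. The sign therefore turns on quantities the article does not give.

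**The case against.** **Data are not discarded.** A reader might infer that the outcome data of withdrawn participants are thrown away. The document does not support that, because the analysis section keeps everything collected before withdrawal. What is missing is later collection.

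**This is a condensed article.** The schedule figure is not shown, and the Adverse events section mentions a final follow-up visit without saying whom it covers. An early-termination assessment is neither stated nor excluded. That objection stands in part: the absence of later scores is inferred from the withdrawal wording and the carry-forward provision. If the full protocol already continues assessments, the change is a clarification.

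**It is not an on-treatment analysis under another name.** A reader might call it that. Carrying forward keeps every randomised participant in the comparison, and the adherent-completer question has its own analysis. That separate analysis also means that ending follow-up of poor adherers is not needed to answer it.

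**Informativeness is not shown.** The safety section reports no excess of side effects over placebo in three psychosis trials, and rare toxicity at much higher doses in another condition. However, the article says that 4000 mg per day has not been studied in schizophrenia. Only *may be informative* is supported.

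**The loss cannot be priced.** It is tempting to compare 13 with 10.4 per arm, which widens a detectable difference by √(13/10.4) = 1.118, about 12%. That charges the whole attrition allowance to these rules, although it includes voluntary losses and is already built into the 52.

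**Ratings after unblinding may be biased.** This is fair. It argues for flagging those ratings, not for leaving them uncollected.

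**Conclusion.** The concern holds in a limited form. As written, the rules end study participation for non-adherence, a related serious adverse event or unblinding, and the article provides for no outcome assessment afterwards. Later PANSS scores, including week 6, are then replaced by carried-forward values or left to a missing-at-random assumption. Because the triggers follow randomisation and may depend on dose or outcome, this weakens the stated ITT analysis.

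No size or direction can be attached. The document does not say how many withdrawals these rules would cause, what happens to symptoms afterwards, or how the arms would differ. The percentages in the working only illustrate that the sign is open. In particular, the inference that carrying forward is necessarily conservative is unsupported: with benefit lost after stopping and no background trend, it is unbiased or too favourable to the drug.

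This does not show an error in the sample size. It is an improvement that should be made, and it is cheap, but it must be in place before the affected visits are missed.

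**What to change.** In Participant withdrawal and Unblinding, separate withdrawal from study medication from withdrawal from outcome follow-up. Leave the clinical criteria for stopping medication as they are; they are not judged here. Then:

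- Continue the scheduled week 2, 4 and 6 assessments for every participant who still consents and has capacity to consent. Those who revoke consent, or are continually unable to give it, leave the study.
- Record the date of and reason for stopping medication.
- Include PANSS scores obtained after stopping in the ITT analysis.
- Flag ratings made after unblinding and examine them in a sensitivity analysis.
- Keep the adherent-completer analysis as the secondary analysis it already is.

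The cost is a small protocol amendment, with ethics approval, and at most a few already planned visits per affected participant in a six-week trial. Participants who decline further visits will still have missing scores, so the method for missing data remains necessary.
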